### Study endpoints

The primary endpoint measures are the csSCV in stage I and the primary venipuncture success rate in stage II. The secondary endpoint measures in stage II are the number of needling attempts for successful venipuncture, venipuncture time, total catheterization time, first-pass success rate, and complication rate.

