If the first attempt at venipuncture fails, the needle is slowly retreated until the needle tip is in subcutaneous tissue. The angle and depth of the needle will be adjusted for the next needle passage, which is dependent on the practitioner’s judgment. If the first practitioner fails to puncture the SCV after three needling attempts, the second practitioner will attempt venipuncture. If the second practitioner also fails at venipuncture after three needling attempts, the case will be classified as a failed SCV catheterization. In addition, if arterial puncture or air aspiration is evidently detected during the procedure, failure of the SCV catheterization will be considered. In cases of failed SCV catheterization, the central venous catheter will be placed in another central vein, such as the internal jugular or femoral vein.

SCV catheterization-related data, such as the number of needling attempts for venipuncture and total catheterization time, will be collected during the procedure. Clinical signs of air embolism, such as abruptly decreased end tidal carbon dioxide concentration and blood pressure, will be noted. Hematoma, a complication of catheterization, will be detected by the attending anesthesiologists primarily through inspection and manipulation of the puncture site and using ultrasonography if necessary. A chest radiograph will be obtained immediately after surgery to detect catheterization-related complications, such as pneumothorax and misplacement of the catheter tip.

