### Measurements

Demographic data will be collected before SCV catheterization in the stage I patients. The right csSCV will be measured in the supine, 20° ipsilateral tilt, and contralateral tilt positions.

SCV catheterization-related data and demographics will be collected from the stage II patients. The data collected includes the success rate of SCV puncture at the first needling attempt (primary venipuncture success rate), the number of needling attempts for successful venipuncture, venipuncture time (time from skin puncture to venous blood aspiration), total catheterization time (time from skin puncture to completion of indwelling catheter insertion), first-pass success rate of catheterization (success rate of catheterization at the first attempt without any complications and technical disturbances, such as failed venous puncture or difficulties inserting the guidewire, dilator, or catheter), overall success rate of catheterization, the rate of puncture on the anterior wall of the SCV, the incidence of rescue mechanical ventilation, and the number of manipulation attempts to insert the guidewire, dilator, and catheter.

Data on catheterization-related complications, including arterial puncture, hematoma, pneumothorax/hemothorax, air embolism, and misplacement of the catheter tip (placement of the catheter tip in a location other than the superior vena cava or right atrium), will be collected during and after the procedure.

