### Statistical analysis

Statistical analyses will be performed with SPSS 21.0 (SPSS Inc., Chicago, IL, USA) and Med Calculator (MedCalc Software, Ostend, Belgium). All continuous variables will be expressed as mean ± standard deviation or median (interquartile range) based on results of the Shapiro-Wilk test. All categorical variables will be expressed as numbers (percent).

In stage I, the cross-sectional areas in the three different positions will be compared to the paired *t* test or Wilcoxon signed-rank test according to the results of the Shapiro-Wilk test. The alpha level of 0.017 (0.05/3) is set to compensate for multiple comparisons (× 3). In stage II, the number of needling attempts for venipuncture, venipuncture time, and total catheterization time between the two groups will be analyzed with the Student’s *t* test or the Mann-Whitney test. The primary venipuncture success rate, first-pass success rate, and complication rate will be analyzed with the chi-square test or Fisher’s exact test. A *P* value < 0.05 is considered significant.

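### Three stage II secondary endpoints are defined by reaching success, so failed catheterizations have no clear value and the default comparison is among successes only

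*Protocol article*

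**What the plan says.** All references are to the protocol article.

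- **Study endpoints** lists five stage II secondary endpoints. Three of them are "the number of needling attempts for successful venipuncture, venipuncture time, total catheterization time"; the others are first-pass success rate and complication rate.
- **Measurements** ends each time at a success event: "venipuncture time (time from skin puncture to venous blood aspiration" and "total catheterization time (time from skin puncture to completion of indwelling catheter insertion". It records the count as "the number of needling attempts for successful venipuncture".
- **Study protocol** expects cases in which those events never happen. After three failed attempts by a first practitioner, a second takes over: "If the second practitioner also fails at venipuncture after three needling attempts, the case will be classified as a failed SCV catheterization". Failure is also to be considered when arterial puncture or air aspiration is evident. The catheter then goes into another central vein.
- **Study protocol**, on data collection, drops the word successful: "such as the number of needling attempts for venipuncture and total catheterization time, will be collected during the procedure".
- **Statistical analysis** drops it too: "the number of needling attempts for venipuncture, venipuncture time, and total catheterization time between the two groups will be analyzed" with Student's t test or the Mann-Whitney test. No value, rank or censoring rule is given for a failed case.
- **Withdrawal, dropout, and discontinuation** says that analyses follow the intention-to-treat principle.

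**The concern.** A patient whose vein is never entered has no venipuncture time as defined. A failed catheterization has no total catheterization time, unless time to the alternative vein is meant to count, which the text does not say. The count depends on which wording is followed. Under the Measurements and Study endpoints wording, a failed case has none. Under the Study protocol and Statistical analysis wording, it has the number of attempts made. On that second reading, a case abandoned for arterial puncture at the first attempt could score 1, the best possible value.

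Neither planned test can use a missing value, so following the text literally means comparing successes with successes. Success comes after randomization, and the trial's hypothesis is that position changes puncture success. The two sets of successes are then no longer the randomized groups. Shorter procedure time is part of the stated hypothesis, and total catheterization time is named in the Discussion as one of the comparisons that will show which position is safer and easier.

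**Working it through.** **1. The plan's own figure.** The Sample size section gives 74.5% in the supine position, a 15% increase, alpha 0.05, beta 0.2 and 100 per group. Read as 15 percentage points, two-sided, unpooled:

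n = (1.960 + 0.842)² × (0.745 × 0.255 + 0.895 × 0.105) / 0.15² = 7.849 × 0.28395 / 0.0225 = 99.1, so 100.

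The pooled formula gives 102. A relative 15% increase would need 200. So 74.5% vs 89.5% is the planned contrast and is used below, with the 110 randomized per group.

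**2. Model for the count.** The documents give no failure rate and no success rate after the first attempt. I assume one success rate r for each of attempts 2 to 6, the same in both arms. With first-attempt success p:

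- P(success at attempt 1) = p
- P(success at attempt k) = (1 − p)(1 − r)^(k−2) r, for k = 2 to 6
- P(failure) = (1 − p)(1 − r)^5

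Failures declared for arterial puncture or air aspiration would come on top; their rate is not given.

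**3. One case in full, r = 0.3.**

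- Failure: supine 0.255 × 0.7^5 = 0.0429; tilt 0.105 × 0.7^5 = 0.0176. Per 110 patients: 4.7 vs 1.9.
- Sum of k × P(success at k): supine 1.4500; tilt 1.1853.
- Mean among successes: supine 1.4500 / 0.9571 = 1.515; tilt 1.1853 / 0.9824 = 1.207. Difference 0.31.
- Mean in all randomized, failure scored 7: supine 1.4500 + 7 × 0.0429 = 1.750; tilt 1.1853 + 7 × 0.0176 = 1.309. Difference 0.44.

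**4. The range.** Differences are supine minus tilt, so positive values favour tilt.

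| r (assumed) | Failures per 110, supine vs tilt | Difference, successes only | Difference, all randomized (failure = 7) |
|---|---|---|---|
| 0.745 | 0.03 vs 0.01 | 0.20 | 0.20 |
| 0.5 | 0.9 vs 0.4 | 0.27 | 0.30 |
| 0.3 | 4.7 vs 1.9 | 0.31 | 0.44 |
| 0.2 | 9.2 vs 3.8 | 0.29 | 0.55 |

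**5. Effect on the test.** Simulated Mann-Whitney power for attempts under the same model (110 per arm, two-sided 0.05, 3,000 replicates), successes only vs failures at the worst rank: 83% vs 84% at r = 0.5, 77% vs 82% at r = 0.3, and 70% vs 83% at r = 0.2.

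The two times were not modelled, because the documents give no distribution for them.

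**The case against.** The strongest reply is that this is a journal article without its analysis plan, and that scoring undefined secondary values is often left to that plan. No section says failed cases will be excluded, and the article commits to intention to treat. That stands against one stronger reading that a reader might infer, namely that the protocol states a successes-only analysis. It does not; the analysis follows by default from the definitions and the tests. The reply does not dispose of the point. The endpoint definitions, the failure rule and the analysis principle are all in the text and do not fit together, and the count is worded in two ways.

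Other limits also stand:

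- Attempts can be counted in a failed case, so for that endpoint the fault is inconsistency rather than a plain restriction to successes.
- A case that fails after venous blood was aspirated still has a venipuncture time.
- A reader might infer that randomization is lost across the secondary endpoints. It is not. First-pass success and complication rate are defined for every randomized patient, as is the primary endpoint. Overall success rate is also collected, so failures remain visible.
- A reader might infer that the better position could come out looking worse. That would need tilt to turn failures into late successes with little or no first-attempt benefit. At the planned rates, the successes-only difference favours tilt for every r tried.
- A tied worst rank treats an early arterial puncture like six missed attempts. That is a real simplification and should be stated.

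**Conclusion.** The point holds in limited form. Three of the five stage II secondary endpoints are undefined or inconsistently defined for failed catheterizations that the protocol itself expects. The default successes-only comparison conflicts with intention to treat.

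The likely harm is dilution of a true benefit. For attempts it is negligible when later attempts usually succeed (0.20 under both analyses at r = 0.745). It reaches roughly half of the difference when they seldom do (0.29 instead of 0.55 at r = 0.2). These sizes rest on an assumed later-attempt success rate common to both arms, on a score of 7 for failure, and on reading the 15% as percentage points. The true failure rate cannot be taken from the documents. The primary endpoint and the sample size are not affected. The change is worth making because it is nearly free and removes a choice that would otherwise be open at analysis.

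**What to change.** 1. Use one definition of the number of needling attempts in Study protocol, Measurements, Study endpoints and Statistical analysis.
2. In Statistical analysis, state that all randomized patients are included and compared by the Mann-Whitney test. Failed cases take the tied worst rank for attempts and total catheterization time. They take it for venipuncture time when venous blood was never aspirated.
3. Keep successes-only times as descriptive summaries, reported beside the overall success rate.

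The cost is a sentence or two in the analysis section and consistent wording elsewhere; no new data are needed. The downside is small: the result is a rank comparison instead of a mean difference in seconds, and all types of failure are ranked equally.

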### Sample size

The right csSCV in the supine position for stage I was reported to be 0.93 ± 0.17 cm^2^ in a previous study [10]. At an alpha level of 0.017 and a beta level of 0.2, a minimum of 15 patients are required to confirm a 15% increase in the csSCV in the ipsilateral tilt position compared to the supine position in the same patient. Considering a 10% dropout rate, 17 patients are needed for stage I.

In stage II, the primary venipuncture success rate has been reported to be 74.5% in the supine position during right SCV catheterization [11]. At the alpha level of 0.05 and a beta level of 0.2, at least 100 patients per group are needed to determine a 15% increase in primary venipuncture success rate in the ipsilateral tilt position. Assuming a 10% dropout rate, 110 patients are needed in each group.

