## Methods

### Study design

This is a two-staged, prospective, single-blind, single-center, superiority, randomized controlled trial. Stage I has a crossover design and stage II has a parallel randomized assignment. This study was approved by the Institutional Review Board of Seoul National University Hospital (number: 1707–110–871, date: 11 September 2017) and registered at ClinicalTrials.gov (NCT03296735 for Stage I and NCT03303274 for stage II). This trial is still being conducted at Seoul National University Hospital. The study protocol is reported according to the Standard Protocol Items: Recommendations for Interventional Trials guidelines (Fig. 1 and Additional file 1). In addition, the final report of this trial will adhere to the Consolidated Standards of Reporting Trials (CONSORT) Statement.

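### Stage I: 15 patients for 80% power rests on an across-patient SD; if that SD is used for the paired differences, the planned two-sided paired t test has about 68% power

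*Protocol article*

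**What the plan says.** The Sample size section of the protocol article starts from one published figure: "The right csSCV in the supine position for stage I was reported to be 0.93 ± 0.17 cm^2^ in a previous study". It then sets the error rates, "At an alpha level of 0.017 and a beta level of 0.2", and concludes that "a minimum of 15 patients are required to confirm a 15% increase in the csSCV in the ipsilateral tilt position". The reference for that increase is each patient's own supine measurement, so the comparison is paired. A 10% dropout allowance takes 15 to 17.

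The Statistical analysis section plans a paired t test for the pairwise comparisons of the three positions, or the Wilcoxon signed-rank test if the Shapiro-Wilk result points that way. The threshold is 0.05 divided by three because there are three pairwise comparisons.

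The article does not give an SD of within-patient differences, a within-patient correlation, the sidedness of the test, or the formula or software behind the 15. Study design calls the trial a superiority trial, which does not settle sidedness.

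**The concern.** A paired test is driven by the SD of the differences between two measurements in the same patient. The 0.17 cm² quoted is a different quantity: the spread of one measurement, in one position, across patients. The two are linked by the within-patient correlation, which is not stated, so a reader cannot get from the stated inputs to 15 without adding an assumption.

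The added assumption that comes closest to 15 also relies on normal quantiles. With about 15 pairs and an alpha of 0.017, replacing the t distribution by the normal makes a material difference.

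At stake is the beta of 0.2 for the Stage I primary endpoint, which tests the trial's proposed mechanism. If power is lower than stated, a non-significant result could be read as 80%-powered evidence against an enlarged vein when it is weaker than that.

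**Working it through.** **Inputs**
- Supine mean 0.93 cm² and SD 0.17 cm²; increase to detect 15%; alpha 0.017; beta 0.2; dropout 10% (Sample size).
- Paired t test or Wilcoxon signed-rank test at 0.017 (Statistical analysis).
- Assumed because not stated: a two-sided test (one-sided also tried), and the SD of differences (range shown below).

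**Effect.** 0.15 × 0.93 = 0.1395 cm².

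**Reproducing 15.** Take 0.17 as the SD of differences. The standardised effect is 0.1395 / 0.17 = 0.8206. The two-sided normal approximation is

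n = (z for 1 − 0.017/2 + z for 0.80)² × SD² / effect² = (2.387 + 0.842)² × 0.17² / 0.1395² = 15.48.

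This is 15 to the nearest whole number and 16 by the usual rounding up. By the same approximation, power at 15 is Φ(0.8206 × √15 − 2.387) = Φ(0.791), about 78.6%. Other routes with the same SD:
- one-sided normal approximation: 13.03, so 14;
- one-sided paired t test: 16, with 78.7% power at 15;
- two-sample formula: 2 × 15.48 = 30.96, so 31 per group, which does not fit.

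The dropout step is right: 15 / 0.9 = 16.7, so 17.

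**Planned t test on the same inputs.** Power comes from the noncentral t distribution with n − 1 degrees of freedom and noncentrality 0.8206 × √n, two-sided at 0.017:

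| Evaluable patients | Power |
|---|---|
| 15 | 67.9% |
| 17 | 75.5% |
| 18 | 78.8% |
| 19 | 81.6% |

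So 19 is the first number to reach 80%. Using 0.05/3 unrounded gives 67.6% at 15 and 75.2% at 17. The row for 17 assumes that nobody drops out, whereas 17 are enrolled so that 15 remain.

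**If 0.17 is the SD in each position.** With equal SDs and within-patient correlation r, the SD of differences is 0.17 × √(2(1 − r)). For the two-sided paired t test at 0.017:

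| r | SD of differences (cm²) | Power, n = 15 | Power, n = 17 |
|---|---|---|---|
| 0 | 0.240 | 36% | 42% |
| 0.3 | 0.201 | 51% | 59% |
| 0.5 | 0.170 | 68% | 76% |
| 0.6 | 0.152 | 79% | 85% |
| 0.7 | 0.132 | 90% | 94% |
| 0.8 | 0.108 | 98% | 99% |

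Using 0.17 directly as the SD of differences is therefore the same as assuming r = 0.5. Power of 80% needs an SD of differences of at most 0.150 cm² with 15 patients (r about 0.61) or 0.162 cm² with 17 (r about 0.55).

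**The case against.** The strongest reply is that 15 is not an arithmetic slip. The two-sided normal approximation gives 15.48, and a one-sided t test falls short by one patient and 1.3 percentage points (78.7% against 80%). The wording shows that the paired design was recognised. That 0.17 was entered as the SD of differences is inferred from how closely it reproduces 15; the article does not say so. The figure used may stand in the full protocol. Repeated measurements of one vein, taken close together in the same anaesthetised patient, could well correlate above 0.61, and then 15 patients would give 80% power or more.

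Most of this stands, and it limits the point. A reader might infer that the real Stage I power is 68%, or that the stated beta has been shown not to be met. The documents support neither: 68% is conditional on an SD of differences of 0.17 and a two-sided test, and the article states neither. It would be inconsistent to object to 0.17 as the SD of differences and then treat the power it yields as the true value.

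What the reply does not remove is that the article presents a mean, an SD, an effect, an alpha and a beta as the basis for a minimum of 15. With that SD, the planned paired t test does not reach 80% at 15, whether two-sided or one-sided, and even the approximation that comes closest rounds up to 16. This is more than a detail left out of a condensed article, because the derivation that is printed does not carry its own conclusion. Nor does anything make Stage II depend on the Stage I result, so the consequence is confined to how Stage I is read.

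**Conclusion.** The point holds in conditional form. The Stage I size and power are supported only by an across-patient SD, while the quantity that a paired comparison needs is not given.

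If 0.17 cm² was used as the SD of differences and the test is two-sided, the type II error with the planned 15 evaluable patients is about 32% (100% − 68%), against the stated 20%. About 11 points of power are lost by using normal rather than t quantiles (78.6% against 67.9%), and 19 evaluable patients would be needed instead of 15. If the test is one-sided, the shortfall is one patient.

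Outside that assumption the power is unknown. Under equal SDs and a two-sided test, the stated 15 is adequate if the within-patient correlation is about 0.61 or more, and clearly inadequate if it is 0.3 or less (51% or lower). The documents do not say which case applies.

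**What to change.** Keep 17 patients and restate the Stage I sample-size paragraph in one of two ways:

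- Give the SD of within-patient differences (or the correlation) that was assumed, with its source and the sidedness of the test. For a two-sided paired t test at 0.017, 15 evaluable patients are enough only if that SD is at most about 0.150 cm².
- If 0.17 cm² was used as the SD of differences, say so, and state power of about 68% with 15 evaluable patients and about 76% if all 17 are evaluable. Add that 80% would need 19 evaluable patients, which is 22 enrolled after 10% dropout (19 / 0.9 = 21.1).

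The cost is the rewording of one paragraph and, under the second option, a less favourable stated power. No new patients are required and the planned analysis does not change.

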### Statistical analysis

Statistical analyses will be performed with SPSS 21.0 (SPSS Inc., Chicago, IL, USA) and Med Calculator (MedCalc Software, Ostend, Belgium). All continuous variables will be expressed as mean ± standard deviation or median (interquartile range) based on results of the Shapiro-Wilk test. All categorical variables will be expressed as numbers (percent).

In stage I, the cross-sectional areas in the three different positions will be compared to the paired *t* test or Wilcoxon signed-rank test according to the results of the Shapiro-Wilk test. The alpha level of 0.017 (0.05/3) is set to compensate for multiple comparisons (× 3). In stage II, the number of needling attempts for venipuncture, venipuncture time, and total catheterization time between the two groups will be analyzed with the Student’s *t* test or the Mann-Whitney test. The primary venipuncture success rate, first-pass success rate, and complication rate will be analyzed with the chi-square test or Fisher’s exact test. A *P* value < 0.05 is considered significant.

## Discussion

This is the first trial to investigate the effects of ipsilateral tilt position on right SCV catheterization by comparing the csSCV and catheterization-related characteristics between the ipsilateral tilt position and the supine position.

Body position can change the csSCV. The Trendelenburg position increases the csSCV [4–7], whereas contralateral rotation of the head and placement of a roll padding under the shoulder decreases it [8, 9]. However, the effects of ipsilateral tilt position on the csSCV during right SCV catheterization have not been clarified. In this trial, we hypothesized that the ipsilateral tilt position during right SCV catheterization would expand the csSCV by impeding blood flow to the heart. We will test our hypothesis by comparing the right csSCV among three different positions (supine, ipsilateral tilt, and contralateral tilt positions).

The csSCV is an essential factor for successful SCV catheterization, particularly when the anatomic landmark-based technique is used. A large csSCV leads to a high success rate of SCV puncture at the first needling attempt, which can increase the first-pass success rate of SCV catheterization and decrease the chance of catheterization-related complications, such as arterial puncture, hematoma and pneumothorax, due to repeated needling. We will compare the primary venipuncture success rate, first-pass success rate, catheterization-related complications, and total catheterization time during right SCV catheterization between the supine and ipsilateral tilt positions to verify the clinical significance of the right csSCV on SCV catheterization.

With respect to mechanical ventilation during central venous catheterization, there is no well-defined consensus. Pneumothorax is a common SCV catheterization-related complication. A recent study showed that the incidence of pneumothorax during infraclavicular SCV catheterization was similar between patients with positive pressure ventilation and those without [11]. In contrast, another study reported that positive pressure ventilation was associated with the high risk of pneumothorax [12]. In this study protocol, mechanical ventilation will be paused during SCV catheterization to minimize the risk of pneumothorax.

In general, the slight-Trendelenberg-down position is often recommended to engorge the subclavian vein and decrease the risk of air embolism during SCV catheterization. In this study, however, SCV catheterization will be carried out in the supine and ipsilateral tilt position without slight Trendelenberg down. Because patients undergoing craniotomy for brain tumor removal are enrolled in this study, we will need to eliminate the possibility of an increase in intracranial pressure associated with the slight-Trendelenberg-down position.

Placing a patient in the ipsilateral tilt position using the operating table is a simple maneuver that can be easily done in an operating room. In this trial, we expect that the ipsilateral tilt position may be advantageous over the supine position during right SCV catheterization in terms of the success rate of catheterization, procedure time, and catheterization-related complications.

Two problems are expected when performing right SCV catheterization in the ipsilateral tilt position: there is a risk of falling and a tendency of the head to tilt towards the ipsilateral tilt position. Surgical belts strapped around the body of the patient and assistance to place the body and head of the patient in the neutral position are additionally needed to prevent such events. For the ipsilateral tilt group, we additionally pay attention to the attachment of a sterile disposable drape to maintain sterility throughout the procedure. After 20° ipsilateral tilt, the skin puncture site tends to fall below a practitioner’s comfort zone. Therefore, the surgical table is elevated until the practitioner can easily access the puncture site. Also, there is a possibility that the ipsilateral tilt position makes venipuncture difficult in some patients, especially those with obesity. However, SCV catheterization in obese patients is difficult even in the supine position. A subgroup analysis to evaluate the effect of body position on the venipuncture rate in obese patients may be helpful in clinical practice for increasing successful SCV catheterization.

In summary, in this trial, we will attest the beneficial effects of the ipsilateral tilt position on the csSCV and primary venipuncture success rate during right SCV catheterization. Furthermore, comparisons of the first-pass success rate, complications, and total catheterization time during SCV catheterization in the ipsilateral tilt position vs. the supine position will help clarify which position is safer and easier for SCV catheterization.

